#### 2.1.2. Enhanced Treatment-as-Usual Control Group

Participants from the enhanced treatment-as-usual (eTAU) control group will receive the usual care that is provided to adults with ADHD across clinical settings in Malaysia, along with a 30 min online psychoeducation webinar on adult ADHD. The participants will be allowed to initiate, maintain, or discontinue a treatment as they wish. We play no role in determining the treatment plan of the participants. However, we will emphasize the importance of seeking treatment as needed from their respective clinicians throughout the trial. The participants will be required to report both pharmacological and non-pharmacological treatments that they have received through an online questionnaire during the trial period. Data from the eTAU control group participants receiving either mindfulness-based intervention or CBT from their treating clinicians during the trial period will be excluded from statistical analysis to avoid data contamination. The participants from the eTAU control group will receive an invitation to participate iMBI upon completion of data collection.

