### 2.2. Study Design

This is a single-blind randomized controlled trial. Participants who fulfil the inclusion and exclusion criteria will be randomly assigned to an 8-week online mindfulness-based intervention plus treatment-as-usual (TAU) group (i.e., iMBI + TAU) or an eTAU control group using a simple randomization technique. Inattention, hyperactivity–impulsivity, and executive functioning of the participants from both the iMBI treatment and eTAU control groups will be assessed at baseline (week 0), immediate post-intervention (week 8), and 1-month follow-up (week 12).

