### 2.11. Data Analysis

Data will be analyzed by using the IBM Statistical Package for the Social Sciences (SPSS) version 27(IBM, Armonk, NY, USA). Multivariate analysis of covariance (MANCOVA) will be employed to assess mean differences of outcome variables at immediate post-intervention and 1-month follow-up between the two groups (i.e., iMBI + TAU vs. eTAU) simultaneously with baseline scores as covariates. Pairwise comparisons will be conducted to identify specific differences between the groups as deemed necessary. Statistical significance is set at *p* < 0.05. The magnitude of the effect size will be reported using Cohen’s *d* value. When necessary, study data will be analyzed using intention-to-treat analysis (ITT). For ITT, the last observation carried forward method will be used to impute missing values or dropouts. We will perform per-protocol analysis to examine the effectiveness of iMBI when implemented in an optimal manner.

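### Controls who receive mindfulness or CBT after randomisation are excluded from the analysis, a rule stated for the control arm only and not reconciled with intention-to-treat

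*Protocol article*

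**What the plan says.** Section 2.1.2 describes the control condition as usual care plus a short webinar. On treatment during the trial it says: "The participants will be allowed to initiate, maintain, or discontinue a treatment as they wish". It adds that "we will emphasize the importance of seeking treatment as needed from their respective clinicians throughout the trial". It then sets the exclusion: "Data from the eTAU control group participants receiving either mindfulness-based intervention or CBT from their treating clinicians during the trial period will be excluded". The stated scope and reason are "excluded from statistical analysis to avoid data contamination".

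Section 2.2 gives the randomised comparison as an "8-week online mindfulness-based intervention plus treatment-as-usual (TAU) group (i.e., iMBI + TAU) or an eTAU control group". Usual care is therefore part of both arms.

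Section 2.11 says of the analysis sets: "When necessary, study data will be analyzed using intention-to-treat analysis (ITT". Missing data are covered by "For ITT, the last observation carried forward method will be used to impute missing values or dropouts". A separate analysis is also planned: "We will perform per-protocol analysis to examine the effectiveness of iMBI when implemented in an optimal manner". That section does not mention the exclusion in section 2.1.2.

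**The concern.** Randomisation makes the arms comparable at baseline, and the analysis keeps that property only if nobody is removed because of something that happened later. This rule removes people for a later event, and it is written for one arm. Controls who obtain CBT or mindfulness may be deteriorating, more motivated, or improving because of the therapy. What remains of the control arm is then a selected group set against an iMBI arm for which no matching selection is stated.

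The rule also changes the comparator. Section 2.1.2 defines control as usual care in which participants may start treatment and are urged to seek it. Deleting those who do so with CBT or mindfulness leaves usual care without those therapies, which is not the condition participants were randomised to.

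The primary objective, the effectiveness of iMBI on symptoms and executive functioning, rests on this comparison. The protocol does not fix the direction of the bias, so it could not be argued away once the data are in.

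**Working it through.** **1. The passages side by side.**
- Trigger: therapy received during the trial, hence after randomisation (section 2.1.2). The bar on CBT for ADHD or mindfulness training in the past 2 years (section 2.6) is an eligibility criterion for both arms and does not cover this case.
- Arm: only eTAU is named. No corresponding rule is stated for iMBI + TAU.
- Scope: statistical analysis, with no analysis set named.
- ITT (section 2.11): an ITT analysis keeps all randomised participants as assigned. Last observation carried forward is there for missing values and dropouts. An excluded control may be neither, having stayed in the trial with outcomes observed. With no exception stated, the rule and ITT cannot both be followed.

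**2. The plan's own numbers.** Section 2.5 gives 45 per arm, 20% attrition and 54 enrolled per arm. 45 × 1.20 = 54, and 54 × 0.80 = 43.2, so about 43 completers per arm. No single effect size is stated. At an assumed d = 0.6, a two-sided t-test with 45 per arm has about 80% power, so 0.6 is used below. The concern does not rest on these figures.

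**3. Bias from deleting a selected subset (illustration).** Assumptions, none of them given in the documents: no true effect; baseline–outcome correlation 0.6, so the residual SD is √(1 − 0.36) = 0.8; help-seeking correlated ρ = 0.3 to 0.5 with the residual course; the share q of controls highest on help-seeking is deleted from 54.

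Bias = ρ × 0.8 × φ(z)/(1 − q), where z is the normal quantile at 1 − q. Standard error = 0.8 × √(1/54 + 1/(54(1 − q))). The two-sided rejection rate uses the normal approximation.

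| q | φ(z)/(1 − q) | Bias, ρ = 0.3 to 0.5 (SD) | Rejection rate under no effect |
|---|---|---|---|
| 2% | 0.049 | 0.012 to 0.020 | 5.1% to 5.2% |
| 5% | 0.109 | 0.026 to 0.043 | 5.3% to 5.9% |
| 10% | 0.195 | 0.047 to 0.078 | 6.0% to 7.8% |
| 20% | 0.350 | 0.084 to 0.140 | 8.1% to 13.7% |

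Example: q = 20%, ρ = 0.5 gives 0.5 × 0.8 × 0.350 = 0.140 SD. The standard error is 0.163, the ratio 0.857, and the rejection rate 13.5% in the direction of the bias plus 0.2% in the other. Simulation of the ANCOVA at 10–20% agrees (about 0.05–0.14 SD and 6–14%).

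**4. Direction.** The excess rejections all lie on the side of the bias. If the deleted controls had the worse course, the excess favours control, and false findings of iMBI benefit fall below the nominal 2.5% (1.2% at q = 10%, ρ = 0.3; 0.2% at q = 20%, ρ = 0.5). If they had the better course, the excess favours iMBI. In particular, if usual-care therapy improves its users by e SD, deleting them worsens the control mean by q × e: 0.10 × 0.3 = 0.03 SD up to 0.20 × 0.5 = 0.10 SD.

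**5. Numbers lost.** The exclusions come on top of attrition. At d = 0.6, power is 78.5% with 43 vs 43, 77.5% with 43 vs 41 (two controls removed), and 73.3% with 43 vs 34 (20% of remaining controls removed).

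**The case against.** The strongest objection is that few controls may be affected. Section 1.2.3 reports 0.03 and 0.01 clinical psychologists per 1,000,000 population in West and East Malaysia, recent CBT or mindfulness is an exclusion criterion, and the trial window is 12 weeks. At 2–5% uptake the bias is at most about 0.05 SD and the type I error hardly moves. This stands as a limit on the size. It does not settle uptake, because section 2.10 recruits partly through a university counselling centre, and low uptake would not justify the rule.

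Four stronger readings are tempting, and the document does not support them:
- That iMBI participants who start outside CBT are kept. The article does not say how they are handled; it only states no matching rule.
- That treatment use is recorded only in controls. The reporting sentence stands in the control-arm section but names no arm, so the text leaves this open.
- That the rule contradicts a firm ITT commitment. ITT is promised only conditionally. The defect is that no exception is stated, and that no unconditional analysis free of the rule is promised either.
- That the rule inflates claims of benefit for iMBI. It may do the opposite, as step 4 of the working shows.

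Nor can the rule be put down to the condensation of a journal article. It is an affirmative instruction, not an omission.

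**Conclusion.** The rule is wrong as written. It is a post-randomisation exclusion, stated for the control arm only, that applies to statistical analysis without limit. It conflicts with the definition of eTAU in its own section and is not reconciled with the ITT analysis in section 2.11. That conclusion rests on the text alone.

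The size is uncertain. It is negligible to small at 2–5% uptake (about 0.01–0.05 SD, type I error about 5–6%) and material at 10–20% (about 0.05–0.14 SD, about 6–14%). The top of that range needs both 20% uptake and a selection correlation of 0.5. Uptake, selection strength, baseline correlation and d = 0.6 are all assumptions, and the direction is not determined. The correction is still needed before analysis, because it is cheap and the bias cannot be repaired once the affected controls are left out.

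**What to change.** Remove the exclusion from the main analysis in section 2.1.2. State in section 2.11 that every randomised participant is analysed in the assigned arm, whatever other treatment was received. State that the treatment-use questionnaire is given to both arms on the same schedule. If contamination is of interest, confine any exclusion to the per-protocol analysis or a sensitivity analysis labelled supportive, with the same rule in both arms (for example, outcomes after starting outside CBT or mindfulness set to missing and multiply imputed).

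The cost is a sentence or two of text and, if it is not already planned, an existing questionnaire extended to the iMBI arm. The downside is that the main estimate will include some dilution from usual-care therapy. That dilution belongs to the comparison with usual care that the protocol sets out to make.

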### 2.2. Study Design

This is a single-blind randomized controlled trial. Participants who fulfil the inclusion and exclusion criteria will be randomly assigned to an 8-week online mindfulness-based intervention plus treatment-as-usual (TAU) group (i.e., iMBI + TAU) or an eTAU control group using a simple randomization technique. Inattention, hyperactivity–impulsivity, and executive functioning of the participants from both the iMBI treatment and eTAU control groups will be assessed at baseline (week 0), immediate post-intervention (week 8), and 1-month follow-up (week 12).

### 2.3. Randomization

A simple randomization technique will be used to allocate eligible participants to either the iMBI treatment + TAU group or the eTAU control group. The present study will use sequentially numbered, opaque, sealed envelopes for randomization [61]. To ensure that the number of participants is balanced between both groups, even if the recruitment of participants ends earlier than expected, a permuted block of four and six will be used. To blind the participants regarding their conditions, they will be informed that they are going to receive an online healthcare program without providing information regarding their treatment condition.

### 2.4. Study Population

As college emerging adults are reportedly facing multiple challenges in life, including mental health problems [16], risky health behaviors [17], and low educational outcomes [62], these challenges could be particularly pertinent to emerging adults with ADHD. Hence, an effective intervention targeting college emerging adults with ADHD is warranted. The study population will be Chinese Malaysian college emerging adults who have met the DSM-5 diagnostic criteria for ADHD, aged 18 to 29 years in Malaysia. Participants will be recruited from universities or colleges in Malaysia.

### 2.5. Sample Size

Sample size estimation is based on a meta-analytic approach. This estimation includes mindfulness-based intervention studies of individuals with ADHD published from 2008 to 2019 [41,52,53,54,55]. Using a power of 80%, *α* = 0.05, and effect size *f* = ½ *d*, the sample size for the present study is estimated. For inattention, Cohen’s *d* ranges from 0.33 to 3.14. For hyperactivity–impulsivity, Cohen’s *d* ranges from 0.24 to 1.32. For executive functioning, Cohen’s *d* ranges from 1.08 to 2.16. For all treatment outcome variables, it is suggested that a sample size of 45 per condition is needed to detect a power of 0.80 and *α* = 0.05. The present study anticipates a 20% attrition rate, so a sample size of 54 participants per condition is needed, totaling 108 participants.

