## Abstract

Attention-deficit/hyperactivity disorder (ADHD), a common neurodevelopmental disorder, often persists into adulthood. In Malaysia, the prevalence rate of hyperactivity symptoms is highest among Chinese Malaysians. There are limited evidence-based treatment options targeting the core symptoms of ADHD, as well as executive functioning. In addition, conventional psychotherapeutic approaches for adults with ADHD have been found to be highly labor-intensive. The present study will evaluate the effectiveness of an online mindfulness-based intervention to reduce inattention and hyperactivity–impulsivity and improve executive functioning among Chinese Malaysian college emerging adults with ADHD. Informed by established literature, we will design an 8-week online mindfulness-based intervention (i.e., iMBI). We will conduct a two-arm randomized controlled trial comparing an iMBI plus treatment-as-usual group (*n* = 54) and an enhanced treatment-as-usual control group (*n* = 54). Outcome measures of inattention, hyperactivity–impulsivity, and executive functioning will be collected at baseline, immediately post-intervention, and 1-month post-intervention. The findings of the present study will not only demonstrate the implementation of iMBI as a new treatment modality but also inform practitioners on the effectiveness of iMBI in reducing the burden of adults living with ADHD.

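### 54 randomised per arm does not leave the required 45 after 20% attrition: the allowance was multiplied on (45 × 1.2) instead of divided out (45 / 0.8)

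*Protocol article*

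**What the plan says.** The sample size section of the protocol article (2.5) moves from a requirement to a recruitment target in two consecutive sentences. The requirement is that "it is suggested that a sample size of 45 per condition is needed" for 80% power at α = 0.05. The allowance and the target follow in one sentence, the second presented as a direct consequence of the first: "The present study anticipates a 20% attrition rate, so a sample size of 54 participants per condition is needed, totaling 108 participants". The Abstract repeats 54 for each arm. The article gives no other attrition rate and no other inflation rule.

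The effect sizes behind the 45 appear only as ranges of Cohen's d: 0.33 to 3.14 for inattention, 0.24 to 1.32 for hyperactivity–impulsivity and 1.08 to 2.16 for executive functioning. No single design value is named, and it is not said whether α is one- or two-sided.

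**The concern.** An attrition rate is a fraction of the people who enter the trial. To finish with 45 after losing 20%, the requirement has to be divided by the retained fraction, 0.80. Adding 20% of 45 to 45 treats the loss as a fraction of the completers, and that always gives too small a number.

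The article's three figures (45, 20% and 54) therefore cannot all hold. If the trial recruits exactly 108 and loses exactly the anticipated share, it is expected to end below its own stated requirement. The 80% power attached to 45 per arm is then not secured.

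**Working it through.** **Inputs**, all from section 2.5 unless noted:

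- Required per arm: 45
- Anticipated attrition: 20%
- Stated target: 54 per arm, 108 in total (54 per arm also in the Abstract)

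**1. Reproduce the stated figure.** 45 × (1 + 0.20) = 54, and 2 × 54 = 108. It reproduces exactly, so the multiplication rule is what was used.

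**2. Apply the allowance as a loss from those randomised.** n = 45 / (1 − 0.20) = 56.25, rounded up to 57 per arm and 114 in total. Rounding does not explain the gap: 56 × 0.80 = 44.8 is still just short of 45, and 57 × 0.80 = 45.6 meets it.

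**3. Check in the other direction.** 54 × 0.80 = 43.2 expected completers per arm, or 86.4 of 108, against the 45 per arm (90 in total) required.

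**4. Attrition that 54 can absorb.** 1 − 45/54 = 0.167, or 16.7%.

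**5. Size of the shortfall.** 57 − 54 = 3 per arm, 6 in total; 6/108 = 5.6% of the planned size.

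**6. Illustration of the effect on power.** This step needs assumptions that the article does not supply: an unadjusted two-sample t-test and a two-sided α of 0.05. Under these, 45 per arm gives 80% power at d = 0.597, so d = 0.60 is used as the implied effect.

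| Completers per arm | Power at d = 0.60 | d detectable with 80% power |
|---|---|---|
| 45 | 80.4% | 0.597 |
| 43 | 78.5% | 0.611 |

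At the exact implied effect (d = 0.597) and 43.2 per arm, power is 78.3% against 80.0%. Steps 1 to 5 do not depend on any of this and hold whatever effect size lies behind the 45.

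**The case against.** The arithmetic itself is hard to dispute. The case on the other side is that it matters little, and it has four parts.

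- **Everyone may be analysed.** Section 2.11 provides for an intention-to-treat analysis with last observation carried forward, which keeps dropouts in the analysis set. This helps only in part. That analysis is conditional, to be done when judged necessary, and a per-protocol analysis is planned as well. Carried-forward values do not restore the lost information. Above all, section 2.5 itself inflates for attrition; if dropouts counted in full, no allowance would be needed.
- **Baseline adjustment may make up the loss.** Section 2.11 plans a MANCOVA with baseline scores as covariates. If the 45 came from an unadjusted calculation, the move from 45 to 43 is offset once the baseline–outcome correlation r satisfies 1 − r² = 43/45, that is r of about 0.21. At an assumed r of 0.3, power with 43 per arm at d = 0.60 would be about 82%. The article does not say whether the 45 already allows for the covariates, or what r might be, so this is possible but cannot be relied on.
- **The power figures are back-solved.** This is correct. The value d = 0.60 and the t-test are the review's assumptions, and the resulting power loss is an illustration.
- **The effect is minor.** This is also correct: about 2 completers per arm, about 2 percentage points of power, and 0.014 in the detectable d.

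The second and third points limit what can be said about power. None of the four makes 54 the number that leaves 45 after 20% attrition.

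**Conclusion.** The concern holds. At the article's own 20% attrition, 54 per arm leaves an expected 43.2, not 45. The number consistent with the two stated inputs is 57 per arm (114 in total), and nothing elsewhere in the article corrects the figure.

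The consequence is modest. Under the assumed d = 0.60 and two-sided t-test, power falls from 80.4% to 78.5%; any gain from baseline adjustment could offset this. In the other direction, section 2.1.2 removes from the analysis those control participants who receive mindfulness-based intervention or CBT from their clinicians. The article does not say whether they are counted within the 20%; if they are not, the control arm could fall below 43.

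The base figure of 45 was taken as given. It cannot be confirmed from the ranges of d alone, and this conclusion does not need it to be.

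**What to change.** Correct the sentence in section 2.5 so that its three figures agree. Either of these wordings keeps the planned 108:

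- 108 randomised with 20% attrition leaves about 43 per arm, giving 78–79% power at d = 0.60, or 80% at d = 0.61. Name the d, the test and the two-sided α as the assumptions.
- 108 randomised retains 45 per arm provided attrition does not exceed 16.7%.

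It would also help to say whether the control-arm exclusions of section 2.1.2 are part of the attrition allowance.

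The cost is one reworded sentence and a slightly less favourable power or attrition statement. No extra participants and no design change are needed. If the investigators regard 45 completers per arm at 20% attrition as a firm requirement, the target becomes 57 per arm (114, six more than planned), and the Abstract must change with it.

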### 2.6. Inclusion and Exclusion Criteria

The six-item Adult ADHD Self-Report Screening Scale for DSM-5 [63] will be employed to identify prospective participants. With respect to the inclusion criteria, participants must have a diagnosis of ADHD established with the Diagnostic Interview for Anxiety, Mood, and Obsessive–Compulsive and Related Neuropsychiatric Disorders (DIAMOND)–ADHD Diagnostic Module [64], must be aged between 18 and 29 years old, and must be proficient in Mandarin. Participants taking psychotropic prescriptions will be allowed to participate if their prescriptions are stable for at least 6 weeks prior to their participation in the present study.

The exclusion criteria for the present study will include (1) history or current presence of nonalcohol and/or nontobacco substance dependence, psychotic illness, bipolar disorder, personality disorders, conduct disorder, chronic suicidal behavior, and self-injurious behavior as reported in the DIAMOND self-report screening questionnaire; (2) nonverbal intellectual ability of percentile rank 25 or below as described in Raven’s Progressive Matrices–Clinical Edition [65]; and (3) received CBT for ADHD or mindfulness training in the past 2 years.

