### 2.8. Sociodemographic Information and Clinical Characteristics

Sociodemographic information (e.g., gender, age, and ethnicity) and clinical characteristics (e.g., subtype of ADHD, comorbidity, date/year of first ADHD diagnosis, use of ADHD medication, and level of adherence to ADHD medication) will be collected for descriptive purposes.

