### 2.10. Study Procedures

Recruitment of participants will take place in different ways. First, participants from the participating university will be randomly recruited. Second, participants will be recruited from the counselling center at the university. Third, participants will be recruited via campus-based online social media sites (e.g., Facebook) and students’ online portal of the participating university. Last but not least, recruitment presentations at the participating university will also be made to recruit participants. We will start to enroll participants in March 2021 by invitation. The trial is expected to begin in May 2021 and end in December 2021.

Interested individuals will receive a study information sheet and will be invited to a screening session to determine their eligibility. Written informed consent will be obtained from all participants. Eligibility of participants will be assessed using screening and diagnostic measures 2 weeks before the program starts. Data collection will be conducted at a designated laboratory. Participants will be required to complete all study measures. Outcome measures, including attention, hyperactivity, and executive functioning (working memory and inhibition), will be collected at baseline, immediate post-intervention, and 1-month follow-up. Figure 1 presents the Consolidated Standards of Reporting Trials (CONSORT) diagram of the present study.

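### Entry bars only CBT given for ADHD, but the control-arm analysis exclusion names CBT with no indication, so an eligible student in CBT for another condition is dropped only if allocated to control

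*Protocol article*

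**What the plan says.** Section 2.6, third exclusion criterion, bars people who "received CBT for ADHD or mindfulness training in the past 2 years". CBT is qualified by its indication; mindfulness training is not.

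Section 2.1.2 sets a rule for the trial period. Control participants "receiving either mindfulness-based intervention or CBT from their treating clinicians during the trial period" have their data removed: these data "will be excluded from statistical analysis to avoid data contamination". CBT carries no indication here. The rule is written for eTAU only, and no counterpart is stated for iMBI + TAU. The same section leaves treatment choices open: "The participants will be allowed to initiate, maintain, or discontinue a treatment as they wish".

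Three other statements bear on who can be enrolled:

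- The psychiatric exclusions in section 2.6 cover substance dependence (alcohol and tobacco aside) and "psychotic illness, bipolar disorder, personality disorders, conduct disorder, chronic suicidal behavior, and self-injurious behavior". Depressive and anxiety disorders are not listed.
- Section 2.8 records "subtype of ADHD, comorbidity, date/year of first ADHD diagnosis" among the characteristics of those enrolled, so comorbidity is expected.
- Section 2.10 gives several recruitment routes, one being that "participants will be recruited from the counselling center at the university".

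**The concern.** The entry criterion and the analysis exclusion address the same exposure with different wording. Someone already in CBT for a condition other than ADHD passes the first and, read literally, fails the second. The failure is known, or could be, before allocation, yet it takes effect only afterwards and only in one arm.

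At stake is the comparability of the analysed groups. Randomisation would spread such people evenly in expectation. The 2.1.2 rule then takes them out of control and leaves them in iMBI + TAU. People in psychotherapy for another condition may well differ from the rest in symptoms and course, so the analysed arms would differ in make-up for a reason that randomisation does not protect against. There is also a smaller cost in control-arm numbers, for which the sample size makes no allowance.

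**Working it through.** **1. Tracing one candidate through the plan.** Take a student with ADHD in ongoing CBT for anxiety, delivered by a treating clinician.

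- Section 2.6, exclusion 1: anxiety is not listed, so not excluded.
- Section 2.6, exclusion 3: the CBT is not for ADHD and there has been no mindfulness training, so not excluded.
- Section 2.6, medication rule: it concerns prescriptions only and says nothing on psychotherapy.
- Section 2.1.2, if allocated to eTAU: the student may maintain the CBT, and the data are then removed.
- If allocated to iMBI + TAU: no removal is stated, so the data stay.

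The same pre-existing exposure leads to different handling by arm. No other criterion closes the gap.

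**2. What is already covered.** Mindfulness training within 2 years is barred whatever its indication, so current mindfulness training is caught at entry. So is current CBT for ADHD. The gap is confined to CBT for another condition.

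**3. Effect on the comparison.** Let p be the share of each arm in such CBT, and δ the difference in mean baseline-adjusted outcome between them and the other participants. Suppose iMBI has no effect. The iMBI arm, analysed whole, has mean m + pδ. The control arm, with these people removed, has mean m. The expected difference is (m + pδ) − m = pδ, not zero: 0.05δ at p = 5% and 0.20δ at p = 20%. The documents give neither p nor δ, so size and direction are open.

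**4. Effect on numbers.** Inputs from section 2.5: 45 per condition, 80% power, α = 0.05, 20% attrition, 54 per condition. The stated 54 is reproduced by 45 × 1.20 = 54. With 20% attrition, 54 × 0.80 = 43.2 remain per arm, slightly below 45 even before any CBT removal. The planning effect size is not stated; solving a two-sided two-sample t-test for 45 per arm and 80% power gives d ≈ 0.597, an inferred value. The share p is an assumption, taken from 0% to 20%. Evaluable controls = 43.2 × (1 − p), against 43.2 in the iMBI arm:

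| p (assumed) | Share of 54 controls | Evaluable controls | Power at d ≈ 0.597 |
|---|---|---|---|
| 0% | 0 | 43.2 | 0.783 |
| 5% | 2.7 | 41.0 | 0.773 |
| 10% | 5.4 | 38.9 | 0.761 |
| 15% | 8.1 | 36.7 | 0.748 |
| 20% | 10.8 | 34.6 | 0.733 |

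Even at 20% the loss is 0.783 − 0.733 = 0.050; at 5% it is 0.010.

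**The case against.** The strongest reply is that section 2.1.2 means CBT given as ADHD care. The paragraph opens with usual care for adults with ADHD and refers to the participants' own clinicians, so CBT there could be the same exposure as in exclusion 3. That reading is possible. The text is silent on indication, so it cannot be asserted that CBT for any reason was intended. It does not say CBT for ADHD either, and an analyst applying the sentence as written would drop the data. On this reading the remedy is a clarification, which is still needed.

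A second reply is that few people are affected. Section 1.2.3 describes a severe shortage of clinical psychologists, which points to little concurrent CBT. The Discussion says that people with significant psychiatric comorbidity will be excluded; that may only summarise exclusion 1, but it too suggests a smaller pool. This stands as a reason to start the range near zero. It does not remove the inconsistency.

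A reader might also infer more than the documents support:

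- That the flaw would persist even if every randomised participant were analysed. It would not, as a bias: background CBT balanced by randomisation is a feature of the population, and equal background therapy in both arms does not by itself shrink the contrast. The harm needs the mismatch and the control-only removal together.
- That students in CBT are concentrated at the counselling centre. It is one of several routes, and nothing says that it delivers CBT or that its staff count as treating clinicians.
- That the plan admits these people knowingly. The gap may simply be unintended.
- That the mismatch could use up the 54 − 45 = 9 margin in both arms. Only control data are removed, and the share is unknown.

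**Conclusion.** The point holds as a mismatch between sections 2.6 and 2.1.2 which, on a literal reading, produces a foreseeable control-only loss after randomisation. Its size is not given in the documents and may be small: about 2.7 of 54 controls for each 5% affected, from near zero upwards. The loss of power is modest over the whole assumed range, and those power figures rest on an inferred d. The more important consequence is that the analysed arms are selected differently, by an amount (pδ) that cannot be judged from the documents. The conclusion rests on reading CBT in section 2.1.2 without an implied indication; if CBT for ADHD was meant, the defect is one of wording only.

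**What to change.** Reconcile sections 2.6 and 2.1.2 so that one definition of disqualifying CBT applies before randomisation. There are two routes, and the choice is for the investigators:

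- **Align at entry.** Ask about current CBT for any indication at screening and again at week 0, and exclude it in section 2.6. Cost: one sentence and one screening question, and a few candidates become ineligible while their CBT is ongoing.
- **Align in the analysis rule.** Limit the CBT named in section 2.1.2 to CBT for ADHD. Cost: a few words, with no loss of eligibility; CBT for other conditions then counts as background treatment in both arms.

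The existing 2-year look-back can stay, and it needs no addition for current mindfulness training. Neither route settles what happens when a control participant starts CBT after randomisation, which section 2.1.2 allows. That belongs to the control-only exclusion itself and needs its own decision.
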